### Intervention

#### Overview

Through the iMove app, participants will receive a series of Sit Less and Move More intervention messages (notifications) to serve as cues to action [21] and increase readiness to engage in activity. A pop-up message will appear on the phone screen with a sound effect when a notification is received. There will be 2 intervention options, which include Sit Less (sedentary interruption and transition to standing) and Move More (walking) for 1.5-3 minutes, approximately equivalent to 500-1000 steps, and a control option (no messages). Participants can switch off the push notification for a certain amount of time on any given day.

A list of messages is provided in Multimedia Appendix 1.

Notifications are adapted to 4 different context dimensions, including time of day, day of the week (weekend vs weekdays), location (home vs workplace), and weather conditions (good or suitable for PA, rainy and cold or not suitable for PA). Notifications are delivered on 5 occasions (decision points) throughout the day and include morning, lunchtime, afternoon 1, afternoon 2, and evening (details are presented in the “Decision Points” section below).

At each decision point, participants are randomized only if they are available (ie, they are not driving, not sleeping, not active already, and are connected to the internet). The following probabilities are used for randomization: 70% in the intervention (35% SB, 35% PA) and 30% as active control at each particular decision point. GPS will assist with the recognition of driving if the user is on the move. A preset time (9 PM to 8 AM) will be considered for rest and sleeping. In addition, both driving and sleeping can be manually modified by users.

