#### Decision Points

A total of 5 decision points, from 8 AM to 8:30 PM, will be selected as shown in Table 1.

**Table 1 table1:** Occasions (decision points) when notifications are delivered.

Decision point	Time
Morning	8 AM to 10:30 AM
Lunchtime	10:30 AM to 1 PM
Afternoon 1	1 PM to 3:30 PM
Afternoon 2	3:30 PM to 6 PM
Evening	6 PM to 8:30 PM

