### Data Collection and Storage

Activity sensor data (sitting, standing, and walking time) and other mobile data (location, weather, and calendar information) will be collected automatically through SORD and iMove and sent to a Deakin University secured server. Participant questionnaire data, including demographics questionnaire and system usability, will be captured digitally using Deakin secured Qualtrics surveys.

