### Proximal Outcome

Time spent sitting (T_sit_), standing (T_s_), and walking (T_w_) within 1 hour after sending the push notification are the proximal outcomes.

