### Data Analysis

#### Primary Analysis

Data from the 22 participants who generated 42 days of expected data, totaling 4620 decision points, will be analyzed. The study days will be continued until we reach the required number of days of data for each individual. Moreover, to deal with missing data at various decision points that could result from Bluetooth issues with the transfer of data or any other reasons (eg, activity states not being recorded), we will impute 0 for all missing minutes of sitting, standing, and walking.

MRT data will be analyzed using the weighted and centered least-squares estimator as previously described [27]. Using this analytical method, time-varying covariates can be handled, and the causal effect can be consistently estimated. Statistical analyses will be performed using R software (R Foundation for Statistical Computing) using the geepack R package.

Primary outcome measures include decision point, day, availability, interventions, and proximal change in activity states (ie, within 1 hour after the intervention is delivered). Overall effects of delivering a suggestion compared with not providing a suggestion on the subsequent 1-hour sitting, standing, and walking behaviors will be assessed. Moreover, linear treatment effects for Sit Less and Move More suggestions will evaluate the interaction between suggestion effects (ie, Sit Less or Move More) and decision points.

Statistics including β estimate, 95% CI, and *P* values will be reported for the average proximal effect as well as the multivariate effect (main effect). Sit less, Move More, and no suggestion (ie, control) conditions will be compared.

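### The primary proximal outcome is called a level in one place and a change in another, and its hour starts at a message that control points never receive; fix one anchored definition and, separately, adjust for the previous hour.

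*Protocol article*

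**What the plan says.** The protocol article words the outcome in three ways:

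- Proximal Outcome section: sitting, standing and walking times "within 1 hour after sending the push notification are the proximal outcomes". This is a level, timed from sending.
- Primary Analysis section, list of primary outcome measures: "proximal change in activity states (ie, within 1 hour after the intervention is delivered". This is called a change and is timed from delivery. No reference period is given.
- Primary Analysis section, next sentence: the effect of a suggestion against none "on the subsequent 1-hour sitting, standing, and walking behaviors will be assessed". This is a level again.

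The Intervention overview makes the third option "a control option (no messages", allocated with probability 0.30. Participants are randomised only if "they are not driving, not sleeping, not active already, and are connected to the internet". On timing, the Decision Points section says "A total of 5 decision points, from 8 AM to 8:30 PM, will be selected as shown in Table 1", and Table 1 then lists five windows of 2.5 hours each.

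The Data Collection and Storage section says that "Activity sensor data (sitting, standing, and walking time) and other mobile data" are collected automatically. The planned estimator is weighted and centred least squares, which the article says can handle time-varying covariates. Missing minutes in any state are to be set to 0.

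**The concern.** There are two separate gaps.

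**Level or change.** An analyst following the Proximal Outcome section would model minutes in the following hour. One following the list in the Primary Analysis section could subtract an earlier period, whose length the article does not state. The two have different variances, so the power of the same 22 participants depends on the reading.

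**Time zero.** The hour is tied to sending in one section and to delivery in another. A no-message point has neither event, and a 2.5-hour window does not supply a clock time. The sensible reading is that the hour starts at randomisation in every condition, but this is not written.

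There is also an opportunity. The sensor collects activity automatically, so the hour before randomisation should usually be available. It comes before treatment assignment, and the planned estimator can take it as a control covariate.

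**Working it through.** **Inputs from the article.** N = 22; 42 days × 5 = 210 decision points per person; availability 0.70; probability of a message p = 0.7; standardised effect 0.13; 5% significance; target power 80%.

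**Assumed, because the article gives no figure.** r, the correlation between minutes in the previous and the following hour, and equal variances in the two hours.

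**Step 1. Reproduce the stated sample size.** With p(1 − p) = 0.7 × 0.3 = 0.21, the noncentrality for a flat effect is

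22 × 210 × 0.70 × 0.21 × 0.13² = 11.48.

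The article does not state the assumed time trend. A two-parameter (linear-trend) test has 22 − 2 − 2 = 18 denominator df. F(2,18) gives power 80.2%, and N = 22 is the smallest N reaching 80%. The stated figure therefore reproduces. A one-df test of a constant effect with three nuisance terms also has 22 − 3 − 1 = 18 denominator df, and F(1,18) gives 89.3%.

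**Step 2. Variance of each version, relative to the raw level (= 1).**

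- Raw change: 1 + 1 − 2r = 2(1 − r). This exceeds 1 when r < 0.5.
- Level adjusted for the previous hour: 1 − r².

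The adjusted level is never worse than the raw level, since 1 − r² ≤ 1. It is never worse than the change, since 2(1 − r) − (1 − r²) = (1 − r)² ≥ 0.

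**Step 3. Power at N = 22, dividing 11.48 by the relative variance.**

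| r (assumed) | Variance: change | Variance: adjusted | F(1,18): level / change / adjusted | F(2,18): level / change / adjusted |
|---|---|---|---|---|
| 0.2 | 1.60 | 0.96 | 89.3 / 71.7 / 90.5% | 80.2 / 58.9 / 81.8% |
| 0.3 | 1.40 | 0.91 | 89.3 / 77.3 / 91.9% | 80.2 / 65.0 / 83.9% |
| 0.5 | 1.00 | 0.75 | 89.3 / 89.3 / 95.9% | 80.2 / 80.2 / 90.5% |
| 0.6 | 0.80 | 0.64 | 89.3 / 94.7 / 97.9% | 80.2 / 88.5 / 94.5% |
| 0.7 | 0.60 | 0.51 | 89.3 / 98.5 / 99.4% | 80.2 / 95.7 / 98.0% |

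**Step 4. Do the versions estimate the same thing?** The previous hour is fixed before randomisation, so subtracting it or adjusting for it leaves the message effect unchanged. In a simulation with a true effect of 0.13 (600 runs at each of r = 0.2, 0.5 and 0.7), the mean estimates of all three versions lay between 0.128 and 0.131. They differ in precision only.

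**Step 5. Does adjustment supply the missing time zero?** No. The previous hour at a no-message point needs the same start time as the following hour. The anchor has to be written down separately.

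**The case against.** The strongest reply is that change is loose wording. No section describes a subtraction or a baseline hour. The phrase is glossed by a post-message window, the next sentence describes a level, and the same list counts decision point, day and availability as outcome measures. This is probably right. The power loss of a change score therefore shows what the ambiguity could cost, and is not a prediction of what the trial will do. The conflicting words still stand in the primary analysis and should be reconciled.

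Second, a reader might infer that message and control hours start at different times and that the comparison is therefore biased. The article does not say so. All three options are randomised at the decision point, which suggests one common start, and an internet connection is required for availability. What stands is that the common start is implied and not stated.

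Third, the choice of covariates may be left to an analysis plan that is not shown. That is fair: the article's silence is not an exclusion, and the covariates are offered as an improvement, not as the repair of an error.

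Fourth, r is unknown. Above 0.5 a change score beats the raw level. The break-even also depends on equal variances: if the previous hour had half the SD of the following hour (assumed), the change variance would be 1 + 0.25 − r, and the break-even would be r = 0.25. Because only people not already active are randomised, r may be low, and adjustment would then gain little. Near 8 AM the previous hour also falls in the rest period: "A preset time (9 PM to 8 AM) will be considered for rest and sleeping". These limits affect the size of the gain and not the validity of the adjustment.

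**Conclusion.** The point holds as a conflict of definition and an unstated time zero, together with a low-cost gain in precision. It does not show bias: level and change target the same causal effect, and nothing in the article says that the windows differ between conditions. Nor does it show that the trial will lose power, since a change score is probably not intended and would lose to the raw level only for r below 0.5.

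Under equal variances, the adjusted level is at least as precise as either alternative for any r from 0 to 1. The gain over the raw level is small at r = 0.2 and about half the variance at r = 0.7. Adjustment settles the level-or-change question, but it does not repair the anchor. All power figures rest on the assumed r and on a flat effect of 0.13.

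**What to change.** 1. **Definition.** State in both sections that the outcome, in all three conditions, is minutes in each state during the 60 minutes after the logged randomisation (decision) time. Log that time when no message is sent as well. Delete the word change, and stop timing the hour from sending or delivery.
2. **Precision, as a separate step.** Include minutes of the same state in the 60 minutes before randomisation, with decision-point slot and study day, as control covariates in the weighted and centred least-squares model.
3. **Missing prior minutes.** Flag unrecorded prior minutes with a missing indicator. This is valid because they precede randomisation. Exempt them from the rule that sets missing minutes to 0, which would otherwise turn an unrecorded hour into a real-looking value.

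The cost is a change of wording, a stored time stamp, a few covariates that should already be recorded and one indicator. If r is low, little is gained and little is lost.

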#### Secondary Analysis

Applying control systems principles [28], matchable-observable linear identification algorithms will be used to estimate linear time-invariant models from iMove intervention data [28]. Behavioral changes, including standing and walking time, will be assessed as a function of the onset, and offset of individual intervention components (ie, messages) and time-variant determinants (eg, contextual factors). Changes to the input variable (eg, behavior change technique) enable estimation and validation of computational models, therefore allowing exploration of personalized models. An individualized mathematical model of standing and walking time (outputs) will be created for Sit Less and Move More messages considering different contextual factors in different models. Also, further analysis will reveal unique intervention messages that generate the most effective behavior change (ie, either increasing standing or walking time) across various contexts.

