### Aims

The primary aim of this study is to assess the effectiveness of theory-based motivational messages for reducing proximal sitting time and increasing proximal standing or walking time (ie, nonsitting time). The secondary aims involve (1) assessing what type of behavioral components (ie, behavior change techniques) are most effective in reducing sitting time and increasing standing and walking time, measured proximally, and (2) determining relevant contextual moderators for reducing sitting time and increasing standing and walking time.

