#### Sample Size

A total of 22 participants are estimated to detect a small proximal treatment effect size of 0.13 for increasing nonsitting time with 80% power at the level of 5% statistical significance. This was based on the assumptions of 5 decision points per day, a constant randomization probability of 0.7, and an expected participant availability of 70% [16].

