## Discussion

### Overview

We present an MRT to evaluate the development of a Sit Less and Move More JITAI intervention in people with T2D [20]. The proximal and distal main effects of the sedentary and PA interventions on reducing sitting time and increasing standing or walking time (ie, nonsitting time), along with their univariate effects, will be evaluated. Moreover, the most effective behavior change technique will be recognized. Furthermore, the most critical contexts (eg, location: home or workplace) in which users are most responsive to interventions will be identified.

Too much sitting is a distinct behavior consideration from too little exercise for increasing the risk of cardiovascular disease [20]. Practical and integrated approaches involving both Sit Less and Move More have been introduced for risk reduction [20]. It is expected that interventions delivering a combination of Sit Less and Move More would add to the overall daily activity of an individual rather than focusing on at least 150 minutes of weekly exercise [20].

To our knowledge, there are no previous MRT studies targeting SB and PA among people with T2D. Other studies have focused on the general public including healthy sedentary adults [14] and university students [29]. The study by Klasnja et al [14] showed that the 6-week MRT intervention (antisedentary or walking vs no suggestion) among healthy sedentary adults (n=44) was effective to increase the average 30-minute step counts (ie, within 30 minutes after the intervention) by 14%. The study by Figueroa et al [29] conducted a 6-week MRT with university students (n=99) to improve their PA level. They showed that receiving the intervention (motivational messages and feedback on step counts vs no suggestion) increased daily steps by 729 steps, but this effect was diminished over time to –33 steps a day. They recommend that future studies need to take into account both user context and preferences [29].

These theory-based MRT studies were mainly focused on walking [14] rather than standing. Incorporating standing into the intervention package could make the Sit Less and Move More concept more practical. Replacing sitting time with standing could be considered a medium in which the most sedentary populations (eg, T2D) may make the initial transition from an inactive lifestyle to a more active lifestyle [30].

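### Moderation by location, weekday/weekend and weather is left to person-by-person models of standing and walking; aim 2 needs a named pooled analysis that includes sitting

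*Protocol article*

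**What the plan says.** The Aims section of the protocol article gives, as the second secondary aim, "determining relevant contextual moderators for reducing sitting time and increasing standing and walking time". The Discussion (Overview) goes further and says that the contexts in which users respond best, such as home or workplace, will be identified. The Intervention section (Overview) lists four context dimensions: time of day, weekday or weekend, location and weather.

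The article describes two analyses.

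- **Primary Analysis.** A weighted and centered least-squares model on all 22 participants, with sitting, standing and walking in the following hour as outcomes. The article notes that this method can handle time-varying covariates. The only interaction it names is between message type and decision point. Decision points are time-of-day windows, so this covers the first of the four context dimensions.
- **Secondary Analysis.** A system-identification method will "estimate linear time-invariant models from iMove intervention data". At what level, and for which outputs, is stated: "An individualized mathematical model of standing and walking time (outputs) will be created for Sit Less and Move More messages". Different contextual factors go into different models. A further analysis, not specified, will look for the most effective messages across contexts; its criterion is again more standing or more walking.

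The Sample Size section plans for a "small proximal treatment effect size of 0.13 for increasing nonsitting time", "with 80% power at the level of 5% statistical significance". That is the average effect, not a difference in effect between contexts.

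**The concern.** Aim 2 and the Discussion ask a question about users as a group: in which contexts do messages work better? For three of the four context dimensions, the method named answers a different question, one participant at a time. A model fitted to one person has few untreated decision points, fewer still once they are divided by context. Contexts that appear important in such models would be hard to tell from chance.

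The outcomes do not match either. Sitting comes first in aim 2, but it is not a named output of the individual models and is not the criterion of the further analysis.

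Messages are randomised against no message at each available decision point, so the data support a pooled estimate of message-by-context moderation. The estimator that would give it is already in the plan. This is a stated choice of method, not a detail left to an analysis plan.

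**Working it through.** **1. The plan's own figure.** Inputs from Sample Size and Other Outcome Measures: 42 × 5 = 210 decision points per person, availability 0.7, randomisation probability 0.7, standardised effect 0.13. In the usual sample-size formula for this design, the noncentrality per participant is

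210 × 0.7 × 0.7 × 0.3 × 0.13² = 0.522, or 11.48 for 22 participants.

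With a two-parameter effect model and a constant effect, the noncentral F test gives 22 to 23 participants (power at 22 about 0.80). A quadratic trend gives 22 to 24. A single-parameter constant effect gives 18. The article does not state its trend, but 22 is reproduced by standard variants. It sizes the pooled average effect only.

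**2. Data per person.** 210 × 0.7 = 147 available points. With the 35/35/30 split this is 102.9 with a message (51.45 of each type) and 44.1 without.

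**3. Main effect within one person** (residual SD = 1, independent errors).

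- Any message versus none: SE = √(1/102.9 + 1/44.1) = 0.180; detectable with 80% power = 2.80 × 0.180 = 0.50 SD.
- One message type versus none: SE = √(1/51.45 + 1/44.1) = 0.205; detectable = 0.57 SD.
- Power for 0.13 SD: 11% and 10%.

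**4. Difference in effect between two contexts.** For a context present in a share s of points, SE = SE(main) / √(s(1 − s)). For s = 0.5 and any message this is 0.180 / 0.5 = 0.36, so the detectable difference is 2.80 × 0.36 = 1.01 SD. Pooling over 22 divides by √22 = 4.69, giving 0.215 SD. The documents give no context shares, so a range is shown. Weekends are 2/7 = 29% of days, close to the 30/70 row if availability is alike.

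| Context split | One person, any message | One person, one type | Pooled 22, any message | Pooled 22, one type |
|---|---|---|---|---|
| 50/50 | 1.008 | 1.150 | 0.215 | 0.245 |
| 30/70 | 1.100 | 1.255 | 0.235 | 0.267 |
| 20/80 | 1.261 | 1.437 | 0.269 | 0.306 |

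Availability matters little to the contrast. At 50% the 50/50 figures for any message are 1.19 SD (one person) and 0.254 SD (pooled); at 100% they are 0.84 and 0.180.

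**5. Power for an assumed moderator size.** The documents give none, so two values are used: 0.13 SD (the size of the planned main effect) and 0.26 SD (twice that). Ranges run over the three splits.

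| Moderator effect | One person, any message | Pooled, any message | Pooled, one type |
|---|---|---|---|
| 0.13 SD | about 6% | 27-40% | 22-32% |
| 0.26 SD | 9-11% | 77-92% | 66-84% |

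**6. Sitting as a complement.** In a fixed one-hour window, sitting is roughly 60 minutes less standing and walking. The identity is not exact: the sensor also records lying (Intervention Platform), and missing minutes of sitting, standing and walking are all set to 0 (Primary Analysis), so the three need not sum to 60.

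**The case against.** The other side has several good points, and they limit what can be claimed.

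- **A reader might infer that the pooled estimator is not used for context at all.** That is wrong for time of day: the message-by-decision-point interaction is planned, with sitting among the outcomes. The gap concerns location, weekday/weekend and weather.
- **A reader might infer that aim 2 cannot be answered for sitting.** The documents do not support this. Standing plus walking is defined as nonsitting time, and a context that moderates one largely moderates the other. The Secondary Analysis also introduces standing and walking as included examples. What stands is that sitting is not analysed directly and the complement is inexact.
- **A reader might take the time-invariant model as a defect in itself**, because the Discussion cites a trial in students with an initial gain in daily steps, "but this effect was diminished over time to" –33 steps a day. Time invariance fixes the response, not the inputs; the same paragraph enters context as a time-varying determinant. Fading over study days is also a separate question from moderation by context.
- **The power figures treat a system-identification model as a two-group comparison.** The article states no test or selection rule for these models and speaks of exploration. The figures therefore measure how much information one person's data hold; they are not the operating characteristics of the planned method.
- **Individual estimates could be combined across people, and the further analysis might do so.** Nothing rules this out, but nothing states it, and the criterion named is again standing or walking.
- **Personal models serve personalisation, a legitimate purpose.** This stands. It is a reason to keep them, not a reason to let them carry a statement about users in general.

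**Conclusion.** The point holds in limited form. For location, weekday/weekend and weather, the only specified analysis is person by person, with standing and walking as outputs, while aim 2 and the Discussion promise a finding about users generally and name sitting. One person's data can detect a 50/50 context difference of about 1.0 SD, nearly eight times the planned average effect of 0.13 (1.01 / 0.13 = 7.8); pooling brings this to about 0.215 SD.

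These sizes assume independent errors, unit residual SD and the context splits shown. Serial correlation would change the per-person figures. Variation between people in the moderator effect and small-sample corrections would raise the pooled ones somewhat. The ratio between the two levels is √22 under the same assumptions.

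It would go too far to say that the trial cannot detect moderators of realistic size, since no moderator size is given, or that pooling settles the matter: at 0.13 SD the pooled power for any message is only 27-40%.

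**What to change.** For aim 2, name a pooled analysis: add message-by-location, message-by-weekday/weekend and message-by-weather terms to the weighted and centered least-squares model already planned. Fit it for sitting as well as for standing and walking, with participant-clustered small-sample standard errors. Base any statement about critical contexts on these estimates and their confidence intervals, not on contexts picked from individual models. Keep the individual system-identification models alongside, labelled as personalised exploration.

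The cost is a few extra models on data and with an estimator already in the plan; no participants or measurements are added. The limit should be written down with the change: the trial was sized for an average effect, and a moderator effect as small as 0.13 SD would probably be missed, so a wide interval must not be read as absence of moderation.
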